**Figure 1 f1:**
[figure not shown]
Flowchart of the research project procedure.

### REA intervention

2.3

The virtual coach, REA, delivers an intervention based on ACT techniques, also inspired by Espen Klausen’s manual (32). The intervention is designed to promote quality of life and perceived psychological well-being while also aiming to prevent psychological distress and PPD in pregnant women through a psychoeducational approach. The module is self-administered and available on both the Android and iOS platforms. All the contents of the dialogues have been developed by a group of psychologists belonging to the Digital Health Research unit of the Fondazione Bruno Kessler (FBK) in Trento and psychologists belonging to the Istituto Pavoniano Artigianelli in Trento, with specific competences in the field of communication, in collaboration with an ACT expert psychologist/psychotherapist, starting from the Handbook (ACT) for the prevention of distress and PPD (32). The content was subsequently reviewed by a senior psychologist from the Operative Psychology Unit of Trento’s Azienda Provinciale per i Servizi Sanitari (APSS).

The intervention spans 8 weeks, with 6 weeks before and 2 weeks after delivery (see **Figure 2**). Each session lasts approximately 20 minutes.

**Figure 2 f2:**
[figure not shown]
Graphical representation of the conversational protocol delivered to women and its chronological structure.

The intervention aims to increase psychological flexibility in women through exercises based on the ACT model, thereby helping to prevent postpartum distress.

The content is delivered through a step-by-step process designed to promote self-awareness, acceptance and normalization of internal states, stress management and an overall improvement in psychological well-being.

The woman will also be provided with a smartwatch to be worn for the duration of the intervention, which collects the following parameters: steps, sleep and heart rate, which can be used for triangulation with the data self-reported by the woman in the questionnaires provided by the chatbot. The objective nature of the parameters collected by the smartwatch (steps, sleep, heart rate) is to serve as a supplementary measure to self-reports, with the aim of facilitating exploratory triangulation of behavioral patterns with psychological changes. It is imperative to note that these parameters will not be utilized for the purpose of making causal inferences or clinical decisions.

#### Technological tools

2.3.1

The study’s technological component is based on the TreC platform, which allows citizens of the Autonomous Province of Trento to access, manage and share information on their health and well-being (33). TreC stands for ‘Cartella Clinica del Cittadino’ (citizen’s medical record) and is a reliable and well-formed platform designed to be a ‘system of systems’ rather than a mere data hub. TreC is designed with a flexible architecture, which enables the collection and management of heterogeneous data and allows the development and use of further subsystems to provide additional and specific functions.

For the present research project, an additional module of the TreC platform, TreC Mamma, is utilized. The application can be downloaded via a specific link sent directly to participants. Authentication takes place via a digital identity service (SPID or CIE).

The smartwatches used to conduct the study are CE-marked, nonmedical devices and GDPR compliant. **Figure 3** shows mockups of the REA intervention with some different sections.

**Figure 3 f3:**
[figure not shown]
Mockups of the REA intervention application with some of its different sections.

### Study outcome

2.4

#### Primary outcomes

2.4.1

The primary outcomes are UX and UE. They will be assessed via questionnaires, namely the User Engagement Scale Short-form (UES-SF) (28), the System Usability Scale (SUS) (29), the Italian version of the Chatbot Usability Scale (ITA BUS B) (30), and the User Mobile Application Rating Scale (uMARS) (31), which will be administered at different time slots through the study, in particular the usability questionnaires will be administered at the end of the third (3 questionnaires) and sixth (end of the study; 4 questionnaires) weeks.

The endpoints to be measured are as followed:

- Scores of the individual items of the questionnaires;- Mean score of the questionnaires;- Differences between the average score values of the individual questionnaires at the different survey times.

The experience of using the app and the virtual coach (REA) and using the intervention itself will be assessed through a semi-structured interview. The endpoints to be measured are qualitative.

#### Secondary outcomes and follow-up

2.4.2

The variable expressing the outcome ‘psychological well-being’ will be assessed by administering the 4 self-report questionnaires, namely the two Whooley’s Questions (24), the Centre for Epidemiological Studies-Depression Scale (25), the Multidimensional Psychological Flexibility Inventory (26) and the 12-Item Short Form Survey (27) at the beginning and end of the psychoeducational intervention (refer to **Table 1** for a detailed overview of the questionnaire adopted). The endpoints to be measured are as follows: a score of the individual items of the questionnaires, the average score of the questionnaires, and the difference between the average score values of the individual questionnaires at the different survey times. At the follow-up appointment, which takes place two months after childbirth, Whooley’s Questions will be administered. If the participant confirms her willingness, the CES-D will also be administered to assess the risk of PPD.

**Table 1 T1:** Summary of the questionnaires administered and their timing.

Screening	At the beginning of the study (week 0)	At the end of week 3	At the end of the study (week 6)	Follow-up (2 months after birth)
Whooley’s Questions	–	–	–	Whooley’s Questions
–	CES-D^a^	–	CES-D	CES-D
–	MPFI^b^	–	MPFI	–
–	SF-12^c^	–	SF-12	–
–	–	SUS^d^	SUS*	–
–	–	ITA BUS B^e^	ITA BUS B*	–
–	–	–	UES-SF^f^*	–
–	–	–	uMARS^g^*	–
–	–	–	–	Qualitative interview
				

a CES-D, Center of Epidemiological Studies-Depression Scale.

b MPFI, Multidimensional Psychological Flexibility Inventory.

c SF-12, Short Form Health Survey 12.

d SUS, System Usability Scale.

e ITA BUS B, Chatbot Usability Scale, version B.

f UES-SF, User Engagement Scale-Short Form.

g uMARS, User Mobile Application Rating Scale.

*These usability questionnaires will be administered the following day, so as not to burden the participant during completion.

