### Design and setting

2.1

REA, the virtual coach developed within the TreC Mamma application, will interact with women for 8 weeks starting from week 25/30 of pregnancy, with one month between the end of session 6 and the beginning of session 7.

Specifically, there will be one psychoeducational session per week with integrated exercises. The woman can choose the day and time that best suits her needs to interact with REA.

At the beginning of the course, REA will administer the 4 self-report questionnaires, namely the two Whooley’s Questions (24), the Centre for Epidemiological Studies-Depression Scale (CES-D) (25), the Multidimensional Psychological Flexibility Inventory (MPFI) (26) and the 12-Item Short Form Survey (SF-12) (27) to establish the baseline level.

After the data collection phase, the intervention will be administered, and its contents will be presented in different formats (text, images, audio, and video tracks).

The questionnaires will be further administered at the end of the intervention to assess whether the women perceived a change in psychological well-being and quality of life. These data will then be triangulated with the parameters collected by the smartwatch.

Four questionnaires will be administered in order to assess usability: User Experience (UX) and User Engagement (UE). Usability and engagement measures include the User Engagement Scale Short-form (UES-SF) (28), the System Usability Scale (SUS) (29), the Italian version of the Chatbot Usability Scale (ITA BUS B) (30), and the User Mobile Application Rating Scale (uMARS) (31). The questionnaires are managed by a microservice within the TreC platform that complies with the requirements and regulations in terms of personal data protection.

After two months, women who have given consent will be undergoing a semistructured interview in order to investigate their experience in using REA and the TreC Mamma application, and to understand how the women felt during the process.

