### Participants, eligibility criteria, and screening

2.2

The study’s target population includes all pregnant women between 25 and 30 weeks of gestation attending the Pregnancy Care Service of the APSS in Trentino. Midwives from the APSS hospital and territorial service were involved in the study to identify women potentially eligible to participate.

Inclusion criteria to participate in the study are as follows: (1) being pregnant, (2) being in a gestational state between the nineteenth and twenty-sixth week, (3) being ≥ 18 years of age, (4) having a smartphone with Internet access, being able to download the app and being able to use it, (5) being a resident of the Autonomous Province of Trento, (6) knowing and understanding the Italian language, and (7) negative Whooley questions.

The exclusion criteria are as follows (1) patients unable to provide informed consent (a prerequisite for participation in the study), (2) inadequate understanding of the Italian language, (3) possible depression, (4) suicidal tendencies, (5) already being in/being in a psychological/psychotherapeutic pathway at the time of recruitment, (6) substance addiction/being in recovery for less than one year, and (7) a clinical history of previous psychological distress.

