The Whooley questions (24) are based on two PHQ-9 (34) items with a yes/no answer mode, administered by the practitioner; a positive test is defined as a positive answer to even one question. The questions are: During the last month, have you often felt down, depressed or hopeless? Have you often felt little interest or pleasure in doing things in the last month?

In pregnancy, for the identification of ‘mixed’ depression the instrument has 100% sensitivity with 68% specificity. In the postnatal period, sensitivity is 100% with specificity 64% for ‘mixed’ type depression and 100% and 44% respectively for major depression.

The Centre for Epidemiological Studies-Depression Scale (CES-D) (25) is a 20-item measure that asks carers to rate how often in the last week they have experienced symptoms associated with depression, such as restless sleep, poor appetite and feelings of loneliness. Response options range from 0 to 3 for each item (0 = rarely or not at all, 1 = sometimes or a little, 2 = moderately or a lot, 3 = most of the time or almost always). Scores range from 0 to 60, with high scores indicating major depressive symptoms. Being an epidemiological instrument, it is particularly short; in fact, the administration takes about ten minutes.

The Multidimensional Psychological Flexibility Inventory (MPFI) (26) is an assessment tool that measures psychological flexibility on several dimensions. It investigates how people adapt their thoughts and behaviors in response to changing situations and challenges. The MPFI focuses on various aspects of psychological flexibility, including openness to experiences, present-moment awareness, and value-driven action. The 12 dimensions of flexibility and inflexibility (according to the Hexaflex model) are assessed through 60 Likert scale items from 1 to 6. The Italian adaptation of the MPFI scale was developed by Landi et al. (35).

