#### Quantitative analysis

2.7.1

Statistical data processing will be conducted via R software, version 4.0.0 (RStudio Team, 2020), IBM SPSS Statistics (IBM Corp, 2020), Stata17 (StataCorp, 2021), and JASP (Jasp Team, 2024).

Categorical variables will be summarized through absolute and percentage frequency distributions, and quantitative variables through appropriate centrality and variability indices.

Descriptive analyses will be calculated for both the psychological variables (depressive symptoms, psychological flexibility and quality of life) and the usability (UX) and user involvement (UE) variables. These analyses will be performed on the variables analyzed at the beginning, during and at the end of the interaction with REA.

The relationships between variables will be analyzed mainly through *ad-hoc* statistical tests, such as the chi-square test, Fisher’s exact test, t-test for paired data or Wilcoxon’s nonparametric tests and the sign test (based on an assessment of compliance with assumptions) to understand the differences between the beginning and the end of the path in the same study sample to the variables under investigation.

In addition, univariate logistic or multinomial regression models will be presented. Finally, to eliminate possible confounding factors, multiple regression models will be proposed in which the effects of the explanatory variables on the outcome variables will be adjusted for possible confounders. For each analysis, statistical significance will be found with a p-value ≤.05.

Multivariate models will include adjustment for potential confounders collected in the protocol, including maternal age, educational attainment, employment status, marital status, previous pregnancies/births (parity), gestational age at enrolment, baseline CES-D, MPFI and SF-12 scores. The extant literature identifies these variables as being associated with perinatal mental well-being and adherence to digital solutions. Sensitivity analyses will explore the robustness of the results with respect to different model specifications and the availability of wearable data (steps, sleep, HR) as exploratory covariates.

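### The Whooley questions are both an entry filter and a beginning-to-end outcome, so they start at or near their floor, and Table 1 contradicts their pre-post use

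*Protocol article*

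**What the plan says.** **Entry.** The inclusion criteria in section 2.2 end with "7) negative Whooley questions". Section 2.5 describes two yes/no items, "administered by the practitioner; a positive test is defined as a positive answer to even one question". A woman who meets the criterion has therefore answered no to both.

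**Outcome.** Section 2.4.2 states that psychological well-being "will be assessed by administering the 4 self-report questionnaires, namely the two Whooley" items, the CES-D, the MPFI and the SF-12, before and after the course. The endpoints are item scores, average scores and the difference in average scores between survey times. The abstract lists the same four instruments as pre-post measures. Section 2.1 says "At the beginning of the course, REA will administer the 4 self-report questionnaires, namely the two Whooley" items, and repeats the set at the end. Section 2.5 refers to four questionnaires at both times without naming the Whooley there.

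**Schedule.** Table 1 shows the Whooley at screening and two months after birth, with no entry at week 0, week 3 or week 6.

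**Analysis.** Section 2.7.1 gives one list of tests (chi-square, Fisher's exact, paired t, Wilcoxon, sign test) "to understand the differences between the beginning and the end of the path in the same study sample", without assigning tests to variables.

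**The concern.** An instrument used to select participants at one extreme of its scale is a poor measure of change in those same participants. Here the scale has two binary items and everyone is admitted at the best possible score. A later measurement can match that score or be worse, so random error alone pushes the group mean in the unfavourable direction. The study has no control group, so nothing in the design separates this drift from real deterioration during the intervention. Section 3 anticipates better well-being after the course, and a measure that starts at its floor cannot show that.

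The text and Table 1 also cannot both be followed. Under the text, the Whooley is given at the start and end of the course. Under the table, the only possible contrast is screening against two months after birth. The mode differs too: section 2.5 has a practitioner administer the questions, whereas section 2.1 has REA do so.

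**Working it through.** The plan gives no sample size or expected change for the Whooley, so there is no stated figure to reproduce for this outcome.

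**Inputs**
- Recruited: 50; drop-out: 20% (section 2.6). Completers: 50 × (1 − 0.20) = 40.
- Antenatal specificity of the Whooley: 68% (section 2.5). It is used here because Table 1 puts the end of study at week 6, and section 2.3 puts the first six weeks before delivery.
- Significance at p ≤ .05 (section 2.7.1).

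**Step 1: the floor.** Score each item 0 (no) or 1 (yes). If screening serves as baseline, every woman scores 0 + 0 = 0.
- Mean change = later mean − 0, which is never below 0.
- Number who can improve = 0, by design.

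If REA repeats the items at the start, improvement is possible only among women who have turned positive since screening. The documents do not say how many that would be.

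**Step 2: positives from error alone.** Assume that all 40 completers are non-depressed and that each screened negative.
- Errors fully stable within a woman: 40 × 0 = 0 newly positive.
- Errors independent between occasions: 40 × (1 − 0.68) = 40 × 0.32 = 12.8.

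Positive correlation between occasions gives a value in between. The documents contain nothing that locates it. Real new cases would add to these counts.

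**Step 3: what the listed tests would do with this outcome.** Take screening as baseline and let k women of 40 turn positive. All discordant pairs run the same way, so the two-sided sign test, which is exact McNemar for paired yes/no data, gives p = 2 × 0.5^k.

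| k of 40 | Sign test / exact McNemar | Fisher, unpaired | Chi-square, unpaired, uncorrected |
|---|---|---|---|
| 4 | 0.125 | 0.116 | 0.040 |
| 5 | 0.063 | 0.055 | 0.021 |
| 6 | 0.031 | 0.026 | 0.011 |

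For k = 4, chi-square treats the data as 0/40 against 4/40: 80 × (0 × 36 − 40 × 4)² / (40 × 40 × 4 × 76) = 2,048,000 / 486,400 = 4.21, p = 0.040. It would declare significant worsening where the paired test gives 0.125. Fisher stays close to the paired test. If the data are instead cross-tabulated as before by after, the row for positive at baseline is empty: chi-square cannot be computed and Fisher returns p = 1.

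Six newly positive women give p = 0.031 on the valid paired test, and six lies inside the 0 to 12.8 range from Step 2. Even the right test could therefore report significant worsening with no true change.

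**The case against.** **The baseline may not be all-negative.** A reader might infer from the entry criterion that every baseline Whooley is negative. That is certain only at screening. Section 2.1 has REA ask the questions again at the start of the course. The inclusion criteria give weeks 19 to 26 and section 2.1 a start at weeks 25 to 30, so up to 30 − 19 = 11 weeks could separate the two and some women could turn positive. This stands, and it softens the claim from exactly at the floor to probably near it. The selection remains.

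**A valid paired test is already listed.** A reader might infer that section 2.7.1 offers no suitable test for paired yes/no data. It names the sign test in the same list, and choosing a test for each variable can be left to an analysis plan. This stands. What is left is a caution against using chi-square or Fisher for this purpose.

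**Little depends on this outcome.** The primary outcomes are usability and engagement. The directional hypotheses in section 3 name only MPFI, SF-12 and CES-D and are called exploratory. Section 4 concedes that any change may not be due to the intervention. This limits the consequence but leaves both the contradiction and the directional bias in place.

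**The follow-up CES-D.** A reader might see a second contradiction, because Table 1 lists it without condition while section 2.4.2 says "If the participant confirms her willingness, the CES-D will also be administered to assess the risk of PPD". That wording can be read as ordinary voluntariness and is compatible with the table. That symptomatic women would be the ones to decline is conjecture.

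**Conclusion.** The point holds in two parts. First, an instrument on which women must be negative to enter is also named as a beginning-to-end outcome, so it starts at the floor if screening is the baseline and probably close to it otherwise, and observed change is tilted towards worsening. Second, the abstract and sections 2.1 and 2.4.2, and by implication the four questionnaires of section 2.5, conflict with Table 1.

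The size is not known. Error alone could make anywhere from 0 to about 13 of 40 women newly positive. The upper end rests on independent errors, no true depression among the 40, and the stated 68% specificity applying unchanged to women already selected as negative. It is a bound under those assumptions and not a forecast.

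A reader might go further and derive predictive values for the postpartum Whooley from the 10–15% prevalence in the introduction. The documents do not support this: that figure is for mothers in general, whereas this sample excludes possible depression and previous psychological distress.

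The outcome is secondary and exploratory, so this should be corrected but does not threaten the study's main aims.

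**What to change.** 1. Remove the Whooley from the pre-post outcomes in the abstract and sections 2.1, 2.4.2 and 2.5 (three questionnaires there, not four), so that the text matches Table 1.
2. Keep CES-D, MPFI and SF-12 as the measures of change.
3. Report any later Whooley descriptively: number newly positive out of the number assessed, with an exact 95% confidence interval and no test against baseline.
4. State in section 2.7.1 that any paired yes/no outcome that is tested will use the sign test already listed (exact McNemar), not chi-square or Fisher.
5. Report how many women decline the CES-D at follow-up.

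This concerns only the outcome list and the analysis. It does not touch the Whooley's role at screening or how a positive answer is handled clinically. The cost is wording plus a count of decliners. No visit, questionnaire or participant is added.

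### Post-intervention measures are fixed at week 6, which is the end of session 6 and not the end of an eight-week programme with two later sessions

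*Protocol article*

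**What the plan says.** **Post measure at the end of the intervention.** Section 2.1, on the psychological questionnaires: "The questionnaires will be further administered at the end of the intervention to assess whether the women perceived a change". Section 2.4.2 gives their timing as "at the beginning and end of the psychoeducational intervention". Section 2.5 repeats this, and section 2.7.1 plans paired tests between the start and the end of the path.

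**Post measure at week 6.** Table 1 lists CES-D, MPFI, SF-12, SUS, ITA BUS B, UES-SF and uMARS in a column headed "At the end of the study (week 6". A footnote moves the four usability scales to the next day. Section 2.4.1 agrees for those scales, giving them at the end of the third and "sixth (end of the study; 4 questionnaires) weeks".

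**Programme length.** Section 2.1 says that REA "will interact with women for 8 weeks starting from week 25/30 of pregnancy". Sessions are weekly, and the same section inserts a break: "with one month between the end of session 6 and the beginning of session 7". On where the weeks fall, section 2.3 says: "The intervention spans 8 weeks, with 6 weeks before and 2 weeks after delivery".

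**After week 6.** Table 1 schedules only Whooley's Questions, CES-D and the qualitative interview, two months after birth. By sections 2.4.2 and 2.5, the CES-D depends on the woman's willingness and the interview on her consent.

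**The concern.** The same assessment is defined in two ways, and the two do not coincide. One definition ties it to the end of the intervention. The other ties it to week 6, which the article also calls the end of the study although sessions and a follow-up still lie ahead.

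Followed as written in Table 1, the pre-post differences in MPFI and SF-12 and the planned post CES-D describe the first six sessions but would be reported as end-of-programme results. The thresholds in section 3 (SUS at least 68, UES-SF at least 3.5, ITA BUS B at least 44 of 55, uMARS at least 4) would be read as a judgement on the whole pathway. On the layout in section 2.3, the part left out is the entire postnatal component. The smartwatch, meant to be worn throughout the intervention, would also run on past the last MPFI and SF-12 with which it is to be triangulated.

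**Working it through.** **Inputs from the article**
- Eight weeks at one session per week (2.1). The number of sessions is not stated. Eight is inferred from 8 × 1 and from the explicit mention of a session 7.
- One month between sessions 6 and 7 (2.1), taken as 4 to 4.34 weeks (30.4 / 7).
- Six weeks before and two weeks after delivery (2.3).
- Start at 25 to 30 weeks of gestation (2.1).
- Final scales at week 6 (2.4.1 and Table 1).

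**Assumption.** Birth at 40 weeks, used only where stated.

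**Step 1: can the intervention end at week 6?**
- End of session 6 = 6 × 1 = week 6.
- End of session 8 = 6 + gap + 2.
  - No gap: 6 + 0 + 2 = week 8.
  - Gap of 4 weeks: 6 + 4 + 2 = week 12.
  - Gap of 4.34 weeks: 6 + 4.34 + 2 = week 12.34.
- With sessions 7 and 8 in the two weeks after a birth at 40 weeks, the end is (40 − start) + 2. That is 10 + 2 = week 12 for a start at 30, and 15 + 2 = week 17 for a start at 25.

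No reading gives week 6 as the end of the intervention. The plan's figure is reproduced only as the end of session 6.

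**Step 2: how much is missed?** At week 6, 6 / 8 = 75% of sessions have been delivered and 2 / 8 = 25% have not.

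**Step 3: which measures come after session 8?**
- None of MPFI, SF-12, SUS, ITA BUS B, UES-SF or uMARS is scheduled again after week 6 (the usability scales: the day after).
- Whooley's Questions, the optional CES-D and the interview are scheduled two months after birth, which is after sessions given in the first two weeks after delivery.

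**Step 4: does the schedule agree with itself?**
- Week 6 falls at 25 + 6 = 31 to 30 + 6 = 36 weeks of gestation.
- Session 7, one month later, falls at 31 + 4 = 35 (35.3 with 4.34 weeks) for a start at 25, and at 36 + 4 = 40 (40.3) for a start at 30.
- With birth at 40 weeks, the interval from the end of session 6 to delivery is 40 − 31 = 9 weeks for a start at 25 and 40 − 36 = 4 weeks for a start at 30.

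A one-month break therefore meets the post-delivery placement only for starts near week 30. For earlier starts, the break stated in 2.1 and the placement stated in 2.3 cannot both hold under this assumption.

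**The case against.** Several points on the other side are fair.

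- **No effectiveness claim is at stake.** A reader might infer that the plan presents a six-session change as the effect of the full programme. The article does not support that. Section 3 calls the psychological outcomes exploratory, the Discussion says that change may not be due to the intervention, and section 4.1 disclaims any evaluation of effectiveness. What remains is a mislabelled time point.
- **Later sessions are not wholly unmeasured.** The two-month CES-D gives a before-after comparison spanning all sessions for willing women, and the interview, which serves a primary objective, covers the experience of REA and the app. But the CES-D is optional and framed as risk of PPD, the interview is qualitative, and neither replaces MPFI, SF-12 or the usability scales.
- **The usability scales were never specifically promised after session 8.** The specific end-of-intervention statements concern the psychological questionnaires. For the usability scales, week 6 can be a legitimate choice, and the error is mainly the label and the scope of the conclusions drawn.
- **Mixed timing is speculative.** A reader might infer that some women would be assessed at week 6 and others after birth. The article describes no separate teams choosing the time: the questionnaires run through the platform in one provincial service, and the only numeric timings agree on week 6.
- **Eight weeks may mean active weeks.** That would remove the conflict between 8 weeks and about 12. It does not bring the end of the intervention to week 6.

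Measuring before birth may also be deliberate, to keep delivery out of the pre-post difference. The article does not say so, and relabelling would accommodate it. Figure 2, which is not shown, may clarify the chronology, but it cannot make the cited sentences agree.

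**Conclusion.** The contradiction is in the text and stands. Week 6 is the end of session 6. The intervention ends at week 8 if the break is ignored and at about week 12 if it is counted, or at weeks 12 to 17 if the last two sessions follow a birth at 40 weeks. The planned post measures of MPFI, SF-12 and all four usability and engagement scales leave out two of about eight sessions (25%) and are not repeated.

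The 25% rests on the inferred count of eight sessions. The mismatch between session 7 and delivery rests on starts at 25 to 30 weeks and, for the intervals to birth, on delivery at 40 weeks.

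A reader might conclude that the primary usability results are invalid or that nothing captures the postnatal sessions. Neither follows. The thresholds can be evaluated after six sessions, provided that they are described that way, and three measures do come later. In an uncontrolled proof-of-concept study this is a should-fix matter of definition and scope.

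**What to change.** 1. In sections 2.1, 2.4.1, 2.4.2 and 2.5 and in Table 1, relabel the week-6 assessment as after session 6 (antenatal phase), and stop calling it the end of the intervention or of the study.
2. Limit the conclusions on pre-post MPFI, SF-12 and week-6 CES-D, and those on the usability and engagement thresholds, to sessions 1 to 6. State that only the two-month follow-up (Whooley's Questions, the optional CES-D and the interview) covers the whole programme.
3. The sponsor must reconcile the passages on total duration, the one-month break and the placement of the last two sessions relative to delivery. Which of them is correct is for the sponsor to say.
4. Optionally, repeat a short in-app set after session 8. It should include UES-SF, since SUS and ITA BUS B alone would leave engagement uncovered. SUS, ITA BUS B and UES-SF together are 10 + 11 + 12 = 33 items.

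Items 1 and 2 cost only wording, and item 3 needs a sponsor decision on the text. Item 4 adds participant burden, which the article tries to limit, and is not needed if the conclusions are restricted as in item 2.
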